### Exploratory aim: patient measures

Table 2 presents patient measures. Patient assessments will be completed at baseline, 12, and 24 weeks. There will be several options to collect the data: [1] study coordinator reads the questions to the patient (either in person or on the phone) and enters the patient responses, [2] the patient completes the assessments in person with a study coordinator, or [3] the patient will take a paper copy home, complete it, and return it at either the next visit, via mail, or scan and email.

### Exploratory aim: Caregiver measures

Caregiver assessments (Table 2) will be completed at baseline, 12 and 24 weeks using the same methods as for patients described above.

### Sample size

#### Aim 1: Implementation outcome (patient level)

The RCT is powered for the aim 1 outcome, ENABLE program uptake, defined as the proportion of patients who complete the ENABLE program. In determining the targeted sample size, we made the following assumptions: [1] an intra-class correlation coefficient (ICC) value of 0.05, [2] alpha of 1% (*α* = 0.01) and 80% power, [3] 20% enrolled patients for whom completion of ENABLE cannot be assessed due to death or becoming too ill to continue with participation, and [4] a proportion of patients completing ENABLE of 0.52 in prior studies. With 24 practice clusters per group and a minimum of 12 patients per practice cluster (down from 15 after 20% unable to assess completion), for a total of 288 patients per group, the detectable difference in ENABLE program uptake is 0.18 (OR = 2.06; RR = 1.33), a medium effect size.

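### The detectable difference of 0.18 does not match the odds ratio of 2.06 and relative risk of 1.33 printed beside it; from the stated 0.52 these correspond to about 0.17

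*Protocol article*

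**What the plan says.** All the figures are in the protocol article, Sample size, Aim 1: Implementation outcome (patient level). Clustering is allowed for by "an intra-class correlation coefficient (ICC) value of 0.05". The error rates are set as "alpha of 1% (*α* = 0.01) and 80% power". The reference is "a proportion of patients completing ENABLE of 0.52 in prior studies". Each arm has 24 clusters, and the cluster size used is "a minimum of 12 patients per practice cluster (down from 15 after 20% unable to assess completion"). That makes 24 × 12 = 288 assessable patients in each arm, as the section also states. The result is one effect on three scales: "the detectable difference in ENABLE program uptake is 0.18 (OR = 2.06; RR = 1.33), a medium effect size". The section gives no second proportion, no formula, and no baseline other than 0.52.

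**The concern.** Once the reference proportion is fixed, a risk difference, an odds ratio and a relative risk are three expressions of one comparison, and any one determines the other two. Here the two ratios agree with each other and with 0.52, but the difference does not agree with them.

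The trial is powered on this outcome, and this sentence is its only statement of the planning effect. The analysis section for Aim 1 says that model-predicted proportions, odds ratios and relative risks will be used for interpretation. Readers will therefore set the results beside these planning values, and the benchmark will differ slightly according to which figure they pick.

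**Working it through.** **Inputs** (all from the Aim 1 sample size section): reference proportion p1 = 0.52; 24 clusters per arm; 12 assessable patients per cluster; 288 per arm; ICC 0.05; alpha 0.01; power 80%. Printed result: difference 0.18, OR 2.06, RR 1.33. Two-sided alpha is my assumption, since the article does not state it.

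**Step 1. Convert between the scales.**

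- From the difference: p2 = 0.52 + 0.18 = 0.70. OR = (0.70/0.30)/(0.52/0.48) = 2.15. RR = 0.70/0.52 = 1.35.
- From the odds ratio: odds = 2.06 × 0.52/0.48 = 2.2317, so p2 = 2.2317/3.2317 = 0.6906. The difference is 0.1706 and RR is 1.328.
- From the relative risk: p2 = 1.33 × 0.52 = 0.6916. The difference is 0.1716 and OR is 2.07.

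The two ratios both point to a difference of about 0.171.

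**Step 2. Can rounding explain it?** Let 0.52 stand for anything from 0.515 to 0.525, and let 0.18 stand for as little as 0.175. The smallest odds ratio is then at 0.515 vs 0.690: (0.690/0.310)/(0.515/0.485) = 2.096. That does not round to 2.06. In the other direction, every pair of proportions that gives an OR rounding to 2.06 and an RR rounding to 1.33, at any baseline, has a difference of only 0.170 to 0.172. Rounding does not reconcile the set.

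**Step 3. Could 0.52 play another role?** As the higher proportion (0.34 vs 0.52), OR is 2.10 and RR 1.53. As the midpoint (0.43 vs 0.61), OR is 2.07 and RR 1.42. Neither gives the printed pair.

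**Step 4. What does the stated design give?** Design effect = 1 + (12 − 1) × 0.05 = 1.55. Effective size = 288/1.55 = 185.8 per arm. Solve for the difference d from 0.52 with 80% power at two-sided alpha 0.01. With the unpooled normal formula:

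d = (2.576 + 0.842) × √[(0.52 × 0.48 + p2(1 − p2))/185.8]

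At p2 = 0.6906 the right-hand side is 3.417 × √[(0.2496 + 0.2137)/185.8] = 0.1706, so the solution is d = 0.1706.

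| Two-sided variant | Difference | OR | RR |
|---|---|---|---|
| Printed | 0.18 | 2.06 | 1.33 |
| Unpooled normal | 0.1706 | 2.061 | 1.328 |
| Arcsine | 0.1722 | 2.076 | 1.331 |
| Pooled normal | 0.1726 | 2.079 | 1.332 |
| Log odds ratio | 0.1743 | 2.096 | 1.335 |
| t, 46 df | 0.1766 | 2.120 | 1.340 |
| Null variance | 0.1771 | 2.125 | 1.341 |
| Continuity-corrected | 0.1777 | 2.130 | 1.342 |

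The unpooled normal formula reproduces both printed ratios, and its difference rounds to 0.17. The last three variants round to 0.18, but their odds ratios are 2.12 to 2.13. One-sided versions give 0.159 to 0.166. No variant returns all three printed figures.

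**The case against.** The strongest reply is that this is one percentage point in one sentence and that nothing in the design turns on it. That stands. The clusters and patients per arm are the same whichever figure is meant. The printed 0.18 is also the cautious one: every two-sided variant above puts the detectable difference at 0.171 to 0.178, so the design has at least 80% power for 0.18 (85% by the unpooled normal formula, 84% by the pooled).

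It also stands that the article names no formula. Only one variant matches both ratios, so calling 0.18 the misprint is an inference. What the document itself shows is only that the figures disagree.

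A reader might go further and infer that the ratios overstate the trial's power, because 0.52 vs 0.691 has about 77% power against a t reference with 46 degrees of freedom. The document does not support that. The analysis section specifies a logit GEE and states no t reference, and an article may leave such detail to a fuller document. Twelve per cluster is given as a minimum. The recruitment section expects 15–27 patients per cluster, and the Discussion allows up to 58 practices. At 27 enrolled (27 × 0.8 = 21.6 assessable), 0.52 vs 0.691 has 92% power by the normal formula and 90% by the t. With 29 clusters per arm of 12 it has 88% and 86%.

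Nor is the medium label an arithmetic error. Cohen's h is 0.35 to 0.37, between the conventional 0.2 and 0.5, and the article names no index or benchmark.

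**Conclusion.** The three figures are inconsistent as printed. From 0.52, a difference of 0.18 is OR 2.15 and RR 1.35, whereas OR 2.06 and RR 1.33 mean a difference of about 0.171. This part is plain conversion and needs no assumption about the test. The size is about 0.01 on the difference and 0.09 on the odds ratio.

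That 0.18 is the wrong entry is likely but unproven. It rests on a two-sided alpha and an unpooled normal formula, neither of which the article states.

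A reader might take the mismatch as a sign that the trial is too small. It is not: 24 clusters of 12 per arm support a detectable difference of 0.17 to 0.18 under all the two-sided variants tried. This is a reporting error in the primary outcome's planning effect, to be reconciled by the authors from their own calculation.

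**What to change.** Rewrite the sentence as one coherent set that names both proportions:

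- If the calculation gave 0.17: 0.52 vs 0.69, difference 0.17, OR 2.06, RR 1.33. Printing the second proportion as 0.691 is safer, because 0.690 exactly gives OR 2.05, while 0.691 gives (0.691/0.309)/(0.52/0.48) = 2.06.
- If the calculation gave 0.18: 0.52 vs 0.70, difference 0.18, OR 2.15, RR 1.35.

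The authors should check their original output to see which applies. The cost is one sentence. The number of clusters, the patients per cluster and the analysis do not change.

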### Randomization

This cluster-randomized trial will be carried out in 3 sequential cohorts of 8–20 practice clusters (4–10 per study arm) to reach the desired sample size of 48 practice clusters. Within each cohort, RCT arm assignment will occur after completion of all required study trainings, including the ENABLE training (Fig. 3). A minimization algorithm for group assignment with random initial start will be used to attempt to simultaneously balance the proportion of rural practices, practice sizes, and minority patients seen within each practice across the two RCT arms. The minimization algorithm will be generated using R software. Study team members and practice cluster members will not be blinded to group assignment or study hypotheses.

### Statistical analysis

All randomized practice clusters will be included in primary comparisons, according to their group assignment, and regardless of their degree of participation in the study. Primary data analysis will include descriptive statistics for baseline practice cluster characteristics, patient characteristics, and outcomes in each RCT arm. We will examine the balance between RCT arms with respect to baseline characteristics (e.g., age, sex, race, cancer type, stage) using effect sizes, such Cohen’s d and Cramer’s. Factors showing non-trivial imbalances between comparators will be used as adjusting covariates in the between-group comparisons. Analysis will be conducted using the latest versions of SAS and R.

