#### Analysis for aim 1: Implementation outcome (patient level)

We will use a logit GEE model with exchangeable correlation structure (to account for clustering within practice) for the binary patient uptake indictor (“yes” if the patient completed a palliative care assessment and all ENABLE program sessions prior to the 12 week assessments and “no” if the patient is still alive but has not completed a palliative care assessment and all six ENABLE program sessions prior to the 12-week assessments), with the group assignment as the main predictor. Model-predicted outcome proportions, odds ratios, relative risks, and confidence intervals for these measures will be used for interpretation. Supplemental analyses using appropriate methods for clustered data will consist of between-group comparisons of the proportion of recruited patients who could not complete the ENABLE sessions due to illness or death, and the number of sessions completed among all patients recruited.

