Like most research, we have encountered challenges during the study start-up period. First, the COVID-19 pandemic significantly impacted the ability for NCORP practices to conduct research and resulted in a need to rely on telehealth. Although most ENABLE activities were already offered via telephone, we modified the protocol so that all study procedures can now be conducted remotely, including the consent process and the comprehensive palliative care assessment. During this time, NCORP practices also expressed concern about the time required to complete the Nurse Coach training. To reduce training burden, the length of the web-based ENABLE Nurse Coach training was reduced from 25 h to approximately 19 h. We anticipate the reduced number of training hours may be beneficial beyond the study given our goal to make the ENABLE training more broadly scalable to nurses and advanced practice providers interested in implementing this EPC program. We also amended the originally required cohort size (*n* = 16) and will permit cohorts of 8–20 practice clusters (4–10 per study arm). To account for this in analyses, we will assess for confounding by cohort. Lastly, although each practice cluster will be expected to deliver ENABLE to 15–27 patients, we recognize that may not happen. To account for this, we will include an option to recruit additional practice clusters (up to 20% of 48 which is 58 practices) and additional cohorts. Despite these challenges, we anticipate the first cohort will launch in the first half of 2021.

There are several anticipated lessons learned from this study. First, to the best of our knowledge, this is the first large-scale study measuring the implementation of early palliative care in community-based oncology practices. To measure implementation, we developed and refined palliative care implementation measures and anticipate that lessons learned will be used to improve these measures. Second, this study not only seeks to identify the superior implementation strategy (VLC or TA), but also to examine the key components of each strategy. To do so, we have developed measures of participation, engagement, and fidelity that have not been applied in other published literature. Lessons learned will inform refinement of the measures and advance the field.

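### Choosing covariates by observed imbalance tends to omit the minimisation factors and cohort, and lets the primary model's covariate set vary with chance

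*Protocol article*

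**What the plan says.** Under Randomization, a minimisation algorithm tries to "simultaneously balance the proportion of rural practices, practice sizes, and minority patients seen within each practice across the two RCT arms". Assignment is made within cohorts: "This cluster-randomized trial will be carried out in 3 sequential cohorts of 8–20 practice clusters (4–10 per study arm"). Trial design adds that half of each cohort goes to each arm.

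The primary analysis reads "We will use a logit GEE model with exchangeable correlation structure (to account for clustering within practice"), "with the group assignment as the main predictor". That section names no other model term.

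The covariate rule stands in the general Statistical analysis section. "We will examine the balance between RCT arms with respect to baseline characteristics (e.g., age, sex, race, cancer type, stage) using effect sizes", and then: "Factors showing non-trivial imbalances between comparators will be used as adjusting covariates in the between-group comparisons". The listed characteristics are examples at patient level, and no size of imbalance is set as the trigger.

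On cohort, the Discussion says, after noting that cohort sizes may now differ: "To account for this in analyses, we will assess for confounding by cohort".

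**The concern.** Balance between arms and prognostic value are separate properties. A factor used to balance the allocation needs to be in the model because it may explain outcome variance, whether or not it ends up unevenly split. A rule that admits only visibly imbalanced factors tends to pass over those the design has balanced. Cohort is the clearest case: split evenly by arm, it will seldom look like a confounder, however much uptake differs between cohorts.

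Two things are at stake. First, if the balanced factors predict uptake and stay out of the model, the standard error does not credit the balance that the allocation achieved. Intervals are then too wide and power is lost. Second, the covariates that do enter are chosen from trial data, against an unstated cut-off, by a team that is not blinded to assignment. Odds ratios are non-collapsible, so a different covariate set means a different estimated quantity.

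**Working it through.** **Inputs from Sample size.** 24 practices per arm, 12 assessable patients each, "an intra-class correlation coefficient (ICC) value of 0.05", alpha 0.01 (two-sided assumed), 80% power, reference completion 0.52, detectable difference 0.18 (OR 2.06, RR 1.33).

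**The plan's own figure.** Design effect = 1 + (12 − 1) × 0.05 = 1.55. Effective size per arm = 288 / 1.55 = 185.8. The normal approximation gives 80% power at 0.693 against 0.52, a difference of 0.173. With a t reference on 48 − 2 = 46 df, the difference is about 0.177. The stated 0.18 reproduces within rounding. At 0.52 against 0.69, which matches the stated odds ratio, the t calculation gives 76% power. That is the yardstick for the power figures below, not 80%.

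**How easily the rule is triggered.** Treat each patient factor as having SE(d) = √(2 / 185.8) = 0.104. Then P(|d| > 0.1) = 0.335 and P(|d| > 0.2) = 0.054. For at least one of the five listed factors:
- cut-off 0.1: 1 − (1 − 0.335)^5 = 0.87
- cut-off 0.2: 1 − (1 − 0.054)^5 = 0.24

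This assumes independent factors, one effect-size measure for all five, and the uptake ICC for patient characteristics. It shows how far the result turns on the missing cut-off.

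**How the rule meets the balanced factors.** For a yes/no practice factor with SD about 0.5 (assumed), a difference of one practice between arms is (1/24) / 0.5 = 0.083 and of two practices 0.167. Good minimisation keeps such a factor below 0.1 or 0.2 often, but not always. An exact half split of a cohort gives zero at practice level.

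**Simulation.** 48 practices of 12 patients, three cohorts of 16, minimisation within cohort on three binary practice factors, total ICC about 0.05. The analysis was a logit marginal model with a bias-corrected sandwich SE and a t reference at 0.01. There were 6,000 null runs and 2,000 runs at a conditional OR of 2.06 per setting. The share of between-practice variance explained by the three factors plus cohort is an assumption. The imbalance rule used an assumed cut-off of |d| > 0.1 on eight candidates (three minimisation factors and five patient factors, one of them weakly prognostic); cohort was not a candidate.

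| Share explained | Type I error: unadjusted / prespecified / imbalance rule | Mean SE ÷ true SD: unadjusted / prespecified | Power (%): unadjusted / prespecified / imbalance rule |
|---|---|---|---|
| 0% | 0.011 / 0.011 / 0.010 | 1.00 / 1.01 | 73 / 71 / 67 |
| 25% | 0.006 / 0.009 / 0.006 | 1.02 / 0.98 | 74 / 76 / 71 |
| 50% | 0.005 / 0.008 / 0.006 | 1.07 / 1.00 | 77 / 82 / 74 |
| 80% | 0.005 / 0.011 / 0.006 | 1.09 / 0.97 | 77 / 87 / 75 |

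Prespecified minus unadjusted power, from unrounded values:
- 0%: 71.10 − 72.95 = −1.9 points
- 25%: 75.70 − 74.10 = +1.6
- 50%: 81.85 − 77.15 = +4.7
- 80%: 86.85 − 77.25 = +9.6

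Monte Carlo error is √(0.01 × 0.99 / 6000) = 0.0013 for type I error and about √(0.75 × 0.25 / 2000) = 1 point for a single power figure, so the smallest gaps are approximate.

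A separate beta-binomial simulation (20,000 replicates, 0.171 difference) gave unadjusted type I error of 0.0060 and 0.0048 at shares of 25% and 50%. Its power gaps were 79.7 − 75.5 = 4.2 and 84.9 − 76.4 = 8.5 points.

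**Stability of the covariate set.** The rule chose about 3 of 8 candidates on average. Nearly all 2^8 = 256 possible sets occurred, and the commonest appeared in 2% to 3% of runs.

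**Small-sample variance.** With an uncorrected sandwich and a z test, the adjusted model rejected a true null in 0.021, 0.025 and 0.022 of 20,000 trials at shares of 0%, 25% and 50%; the unadjusted model rejected in 0.015, 0.012 and 0.009. A repeat check of the adjusted model gave 0.022 to 0.024 uncorrected, against 0.009 to 0.012 with a corrected SE and t reference.

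**The case against.** A reader might infer that the primary model excludes the minimisation factors and cohort and that its confidence intervals are simply wrong. The article does not support that.

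- Calling group assignment the main predictor does not rule out other terms, and a full covariate list is commonly left to an analysis plan, which is not shown here.
- Cohort is not ignored: the Discussion commits to checking it for confounding.
- Minimisation aims at balance without guaranteeing it, cohorts may be as small as 8 practices, and practices will enrol different numbers of patients. The factors can therefore be uneven among analysed patients, and the rule will sometimes pick them up, as it did in simulation.
- The standard-error problem is conservative, and absent if the factors do not predict uptake.

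A reader might also infer that selecting on imbalance inflates type I error, or that the rule by itself pulls power below the planned 80%. The first did not occur in simulation (0.006 to 0.010). The second misreads the yardstick, because the simulated odds ratio corresponds to about 76% power before any covariate question arises.

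Looking at imbalance also has a purpose in this design. Unblinded practice staff recruit the patients, so patient-level differences may reflect differential recruitment. That stands, and it argues for keeping the comparison as a check.

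What survives is the rule itself. It is stated outright, it governs the primary comparison, and it uses imbalance where prognostic value and the allocation design should decide.

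**Conclusion.** The point holds in a limited form. The rule tends to omit the factors on which the allocation was balanced and makes the covariate set, and so the odds ratio estimated, depend on chance and an unstated cut-off. Under the assumed 25% to 80% variance share, the cost of leaving the factors out is a conservative test: type I error about 0.005 to 0.006 instead of 0.01, standard error about 2% to 9% too large, and power about 2 to 10 points below prespecified adjustment. At a share of zero there is no distortion, and adjustment costs about 2 points of power.

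These sizes rest on assumed variance shares, equal practice sizes and, for the selection results, one assumed cut-off and candidate list. The article gives none of them. Should-fix: the primary estimate is affected, but modestly and in the conservative direction.

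**What to change.** Prespecify the primary GEE as arm + cohort + rurality, practice size and minority share, plus a short fixed list of prognostic patient covariates if wanted. Name a bias-corrected sandwich variance and a t reference based on the number of practices. Without that correction, the added practice-level terms would raise type I error to roughly twice nominal. Report standardised proportions, relative risk and risk difference from this model; the article already plans model-predicted proportions and relative risks.

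Move the imbalance-triggered adjustment to a labelled sensitivity analysis with a stated cut-off, where it remains useful for detecting differential recruitment.

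Cost: a change of analysis wording, best made before outcome data are seen. The data are already held for the allocation. With one term per minimisation factor and three cohorts, the model spends 3 + 2 = 5 practice-level degrees of freedom out of 48. Each additional cohort, which the Discussion allows, would use one more.

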#### Analysis for aim 1: Implementation outcome (patient level)

We will use a logit GEE model with exchangeable correlation structure (to account for clustering within practice) for the binary patient uptake indictor (“yes” if the patient completed a palliative care assessment and all ENABLE program sessions prior to the 12 week assessments and “no” if the patient is still alive but has not completed a palliative care assessment and all six ENABLE program sessions prior to the 12-week assessments), with the group assignment as the main predictor. Model-predicted outcome proportions, odds ratios, relative risks, and confidence intervals for these measures will be used for interpretation. Supplemental analyses using appropriate methods for clustered data will consist of between-group comparisons of the proportion of recruited patients who could not complete the ENABLE sessions due to illness or death, and the number of sessions completed among all patients recruited.

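### The primary outcome requires survival for 'no' but not for 'yes', so a patient who dies before week 12 is analysed only if the program was completed

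*Protocol article*

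**What the plan says.** The section Analysis for aim 1 defines the binary outcome for the logit GEE. A patient is 'yes' "if the patient completed a palliative care assessment and all ENABLE program sessions prior to the 12 week assessments". A patient is 'no' "if the patient is still alive but has not completed a palliative care assessment and all six ENABLE program sessions" by the same time point. Only the second definition mentions survival.

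Three other places in the article bear on who is counted:

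- The abstract (Methods) gives the outcome as the share of eligible patients who complete. The Primary aim section gives it as the share of patients who complete. Neither sets a survival condition.
- The aim 1 sample size section allows for "20% enrolled patients for whom completion of ENABLE cannot be assessed due to death or becoming too ill to continue with participation" and so plans on "a minimum of 12 patients per practice cluster (down from 15 after 20% unable to assess completion").
- The Statistical analysis section says: "All randomized practice clusters will be included in primary comparisons, according to their group assignment, and regardless of their degree of participation in the study".

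The aim 1 analysis adds two supplemental between-arm comparisons: the proportion who could not complete because of illness or death, and the number of sessions completed among all recruited patients.

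**The concern.** Among patients who die before the 12-week assessments, completers enter the model as successes and non-completers drop out of it. The outcome therefore helps to decide its own denominator, and it does so after allocation. Yet the status of the dropped patients is not in doubt: the contact log documents each session, and someone who died before the sixth session did not complete.

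The sample size and analysis sections also disagree about living patients who become too ill to continue. The first puts them among those who cannot be assessed; the second makes them 'no'. If the first reading were applied in the analysis, a practice's judgement of who is too ill would help to decide who is analysed.

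Loss before completion could differ between arms. Practice staff, who know their arm and the hypotheses, identify and consent the patients. The VLC arm also receives quality-improvement instruction and written feedback, which could affect who is referred and how soon sessions start. A difference in loss would then move the primary contrast even where the strategies do not differ in getting patients through the program.

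**Working it through.** **1. The plan's own figure.** Inputs from the sample size section: 24 clusters per arm, 12 assessable patients each (288 per arm), ICC 0.05, alpha 0.01 (taken as two-sided), 80% power, reference proportion 0.52.

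- Design effect: 1 + (12 − 1) × 0.05 = 1.55. Effective n: 288 / 1.55 = 185.8 per arm.
- The unpooled two-proportion formula gives a detectable difference of 0.171, OR 2.06, RR 1.33. These are the stated OR and RR.
- With a continuity correction, 0.52 versus 0.70 needs 182 × 1.55 = 282 per arm, close to 288, so the stated 0.18 is also recovered.
- 0.52 + 0.18 = 0.70 implies OR 2.15 and RR 1.35, so the stated ratios belong to a difference of about 0.17. This does not affect the present point.

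The calculation rests on the reduced set (12 of 15), so the exclusion is built into the design.

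**2. What the definition estimates.** Let A be completion among all recruited patients and L the share who die before completing. Living non-completers are counted as 'no', as the analysis section says. The analysed proportion is

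P = A / (1 − L).

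Let q be completion among survivors, d the share dying by week 12, and c the share of those deaths that follow completion. Then A = q(1 − d) + dc and L = d(1 − c). The article gives no separate death rate, so d and c are assumptions.

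**3. Equal completion among survivors** (q = 0.52 in both arms; d = 10% versus 20%).

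| c | P at d = 10% | P at d = 20% | Gain in P for arm with more deaths | Difference in A |
|---|---|---|---|---|
| 0 | 0.520 | 0.520 | 0 | −5.2 points |
| 0.15 | 0.528 | 0.537 | +0.9 points | −3.7 points |
| 0.30 | 0.535 | 0.553 | +1.8 points | −2.2 points |
| 0.52 | 0.546 | 0.575 | +2.9 points | 0 |

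For c = 0.30 and d = 20%: (0.52 × 0.80 + 0.20 × 0.30) / (0.80 + 0.20 × 0.30) = 0.476 / 0.860 = 0.553. A wider gap of 10% versus 30% deaths gives +2.1 to +6.1 points for c from 0.15 to 0.52.

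**4. Equal completion among all enrolled** (A = 0.52 in both arms; L = 10% versus 20%).

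- 0.52 / 0.90 = 0.578 and 0.52 / 0.80 = 0.650, a difference of 7.2 points.
- With L = 10% versus 15%: 0.52 / 0.85 = 0.612, a difference of 3.4 points.

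**5. Equal loss patterns.** If A and L are the same in both arms, P exceeds A by the same factor 1 / (1 − L) in each. The level is too high, but no difference is created.

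**6. Power if completion among all recruited became primary.** Take 360 per arm (24 × 15), design effect 1 + 14 × 0.05 = 1.70, and effective n = 360 / 1.70 = 211.8. Scale the proportions by 0.8, as if the whole 20% counted as 'no' in both arms: 0.8 × 0.52 = 0.416 and 0.8 × 0.70 = 0.560. Power is about 65%. The same formula without continuity correction gives 84% for the planned analysis at 0.52 versus 0.70.

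**The case against.** The strongest reply is that the plan openly chose an outcome among assessable patients and sized the trial on it. On that view the 7 points are not spurious. If 52% of all enrolled complete in both arms but more die first in one, then among those who completed or lived, that arm did have the higher completion. Holding survivor completion equal instead gives at most 2.9 points for the same 10% versus 20%.

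Nor does the article give grounds for expecting a gap in deaths. Its 20% combines death and illness, eligibility requires an expected survival of at least 6 months, and both arms deliver the same program after the same training.

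Counting deaths as 'no' is not neutral either: in step 3 it moves the contrast by 0 to 5.2 points against the arm with more deaths. The plan also adjusts for non-trivial baseline imbalances and compares illness or death, and sessions among all recruited, between arms.

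All of this limits the size of the problem and argues against insisting on a new primary outcome. It does not explain why survival is required for one category only. Neither supplemental comparison analyses completion among all recruited patients, so a reader could see a difference in deaths but not its effect on the primary result.

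**Conclusion.** The point holds as a defect in the outcome definition, with a modest and conditional effect. Under 10% versus 20% deaths, the distortion is 0 to about 3 points with equal completion among survivors. It is up to about 7 points with equal completion among all enrolled and those percentages dying before completion. The design difference is 17 to 18 points. The death rates, and the share of deaths that follow completion, are assumptions. If loss is the same in both arms, the contrast is essentially unaffected.

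Three stronger readings might be inferred but are not supported:

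- That the trial will report a false benefit. That needs a difference in loss between arms which the article neither states nor implies, and the effect alone falls well short of 0.18.
- That the rule breaks the intention-to-treat statement. That statement concerns practice clusters, not patients.
- That practices can stretch the completion window through the 12-week questionnaire. The abstract ties completion to 12 weeks and Table 2 places the assessment at 12 weeks; visit windows are detail an article leaves to the full protocol.

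**What to change.** 1. In Analysis for aim 1, apply one survival rule to both 'yes' and 'no'.
2. Reconcile that rule with the abstract, the Primary aim and the aim 1 sample size section, including the status of living patients who become too ill to continue.
3. Pre-specify a second GEE, reported beside the primary one, of completion among all recruited patients with death before completion counted as 'no'.

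The third step is needed even if survival is required for both categories. That rule gives a zero difference under step 3 of the working. It leaves step 4 unchanged if all completers survive to week 12.

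The cost is revised wording, one extra model on completion data the plan already collects, and a lower reported completion proportion in the all-recruited analysis. Making that analysis primary is optional. It is a choice of estimand, and the power statement would then have to be redone: about 65% at the planned effect under the assumptions in step 6.
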